# Intensive group-based cognitive therapy in patients with cardiac disease and psychological distress—a randomized controlled trial protocol

**DOI:** 10.1186/s13063-021-05405-3

**Published:** 2021-07-16

**Keywords:** Coronary heart disease, Cardiac rehabilitation, HADS, Depression, Anxiety, Psychological distress, Cognitive therapy

## Abstract

**Background:**

Many patients with coronary artery disease (CAD) and valvular heart disease (VHD) suffer from psychological distress. Such stress is associated with increased morbidity, reduced quality of life and delayed return to work. European guidelines emphasize recognition and intervention, but evidence-based treatment options are limited and perceived as costly. The present study will test the effect of brief, group-based cognitive therapy as an adjunct to usual cardiac rehabilitation in a randomized design.

**Methods:**

A total of 148 patients with CAD and/or VHD after surgical intervention and concomitant psychological distress (defined as HADS anxiety (A) or depression (D) score ≥8) will be randomized to either usual out-patient cardiac rehabilitation (CR) comprising an 8-week multidisciplinary programme or usual care supplemented by five group-based cognitive therapy sessions performed by trained CR nurses. A structured, standardized treatment manual will be used. Patients will be randomized 1:1 at three different sites. Additionally, a non-randomized sub-group of 40 matched patients without signs of psychological distress will be followed to investigate spontaneous variation in HADS. The primary outcome is Hospital Anxiety and Depression Score (HADS). Secondary outcomes are adherence to cardiac rehabilitation (CR), health-related quality of life measured by HeartQoL, time to return to work, adherence to lifestyle interventions and cardiovascular readmissions. Patients are followed up for 12 months.

**Discussion:**

To our knowledge, this is the first randomized controlled trial (RCT) on patients with cardiac disease with an intensive group-based programme of cognitive therapy performed by CR nurses, which makes it affordable and widely implementable. The outcome will elucidate the feasibility and effect of cognitive therapy as an adjunct to CR in patients with post-surgery CAD and/or VHD and psychological distress and could possibly benefit patients with other heart conditions as well. The clinical trial complies with the Declaration of Helsinki. The trial has been approved by The Regional Research Ethics Committee (file number H-16042832) and The Danish Data Protection Agency. The results will be disseminated as original research in peer-reviewed manuscripts.

**Trial registration:**

www.clinicaltrials.govNCT04254315. Retrospectively registered on 30 January 2020.

The best treatment for cardiac patients with psychological distress is uncertain, but cognitive behavioural therapy (CBT) may be an effective option. A recent systematic review and meta-analysis [13] concluded that CBT significantly reduced both depression and anxiety and improved QoL compared with controls. Group-based cognitive therapy may be a cost-effective option that can be delivered by specially trained nurses as part of a CR programme. A few studies have reported the effect of group-based CBT on psychological distress in patients with cardiac disease. In a multi-centre RCT [14], 151 unselected patients with cardiac disease received cognitively based group therapy for 12 weeks and obtained a significant additive effect on top of standard CR on a combined endpoint of stress management, cardiac biomarkers and physical activity compared with standard CR alone. Another trial with a 20-week intervention found a similar effect [15]. However, although CBT seems effective, it is still not widely implemented in CR. A main barrier is the perceived need for a comprehensive, time-consuming intervention, which is not possible in the context of a standard CR programme. Therefore, the aim of this trial is to investigate whether brief, group-based CBT integrated in CR and delivered by cardiac nurses can reduce the level of psychological distress in patients with cardiac disease.

## Methods

### Aim

The aim of the study is to develop an efficient and cost-effective model for the use of intensive group-based cognitive therapy to address psychological distress in patients with newly diagnosed CAD and/or surgically treated valvular heart disease (VHD) and concomitant psychological distress.

### Design

The study is a multi-centre, prospective, randomized clinical trial in patients with newly diagnosed CAD and/or surgically treated VHD and concomitant psychological distress defined as HADS (HADS A (Anxiety) or D (Depression) ≥ 8) and part of the work force. Patients with HADS D ≥ 11 and Beck Depression Inventory (BDI) > 17 are evaluated by a psychiatrist to ensure that patients with severe depression or other psychiatric diagnoses are not included in the study. Additionally, 40 patients with HADS score < 8 at their first visit to CR will be followed for spontaneous variation in HADS score at 3 and 6 months to determine whether screening at the first visit to CR is the optimal time at which to identify patients with psychological distress.

### Participants

The trial is a multi-centre trial planned to include 188 patients from three departments of cardiology. The main trial includes 148 randomized patients. We will also include a non-randomized subgroup of 40 matched patients (relative to inclusion and exclusion criteria) without signs of psychological distress to investigate spontaneous variation in HADS scores over time.

Inclusion criteria are:
Referred to CR and accepting CRPatients with newly diagnosed CAD and/ or surgically treated VHDHADS score > 8 for HADS-A and/or HADS-DAge < 65 yearsAble to speak and understand Danish

Exclusion criteria are:
EF < 35%Other serious comorbidity expected to have a serious impact on life expectancyKnown abuse of alcohol or euphoric drugsKnown more serious psychopathology such as schizophrenia, bipolar disorder, severe personality disorder and treatment with psychoactive drugs

### Trial procedure and randomization

Consecutive patients discharged from the hospital with newly diagnosed ischaemic heart disease and/or surgically treated VHD will be screened with HADS at their first visit to CR.

If a patient decides to participate in the study after having received written and verbal information from a research nurse, an informed consent form is signed and the patient is randomized to either (1) CR and intervention consisting of five sessions of CBT or (2) CR alone (Fig. 1).

**Fig. 1 Fig1:**
[figure not shown]
The trial diagram. Flow of patients. Participants in the intervention group follow CR and five sessions of CBT therapy and the control group follow standard CR

Randomization is performed by an independent researcher, and the randomization programme is kept in a secured, logged hard disk. STATA II, the Ralloc programme, permuting random block sizes of 2, 4 and 6, respectively, is used for randomization. Before randomization, baseline data are collected (see Table 1).

**Table 1 Tab1:** Schedule of enrolment, intervention and assessments

	Study period (months)								
	Baseline	Intervention (allocation) Group-based therapy (5 weeks)					Post-allocation (months)		Close-out
Timepoint	0	0	1 week	2 weeks	3 weeks	4 weeks	3 months	6 months	12 months
**Enrolment**									
**Eligibility screen**	x								
**Informed consent**	x								
**Allocation of patients**	x								
**Intervention**		x	x	x	x	x	x	x	
**Control**							x	x	
**Follow-up visit**							x	x	
**Assessments**									
**Background**									
Cohabitant	x						x	x	
Level of education	x								
Employment status	x						x	x	
Sick leave	x						x	x	
Return to work	x						x	x	
Index event	x								
**Clinical measurements**									
Weight	x						x	x	
Heart rate	x						x	x	
Blood pressure	x						x	x	
ECG	x						x	x	
Biochemical screening	x						x	x	
NYHA classification	x						x	x	
CCS classification	x						x	x	
**Medication**	x						x	x	
**Comorbidity**									
History of heart disease	x								
Chronic obstructive pulmonary disease	x								
Kidney disease	x								
Depression	x								
**Risk factors**									
Hypertension	x								
Dyslipidaemia	x								
Diabetes mellitus	x						x	x	
Family history	x								
Smoking	x						x	x	
Physical activity	x						x	x	
Rehabilitation received							x	x	
**Questionnaires**									
HADS	x						x	x	
HeartQol	x						x	x	
Psychosocial status	x						x	x	
**Cardiovascular readmission**									x

Both the intervention and the control group will receive usual care in interdisciplinary CR.

As our patients are still part of the work force, the follow-up visit must fit with their working schedule to reduce potential loss to follow-up. We therefore accept considerable flexibility in the scheduling of follow-up appointments. The patients receive an email or SMS as a reminder before their appointments. If they do not meet for the scheduled appointment, they will be contacted by telephone.

### SPIRIT trial schedule

This paper presents the detailed protocol for the trial “Intensive group-based cognitive therapy in patients with cardiac disease and psychological distress”. The trial is described in accordance with the current SPIRIT guidelines (Standard Protocol Items: Recommendations for Interventional Trials [16]. Results will be reported following the CONSORT (CONsolidated Standards Of Reporting Trials) guidelines for non-pharmacological interventions [17].

### Method to define psychological distress

Psychological distress in patients with cardiac disease has formerly been identified by symptoms of anxiety and depression and identified with HADS [18–23]. HADS is a 14-item questionnaire that assesses anxiety and depression levels in medically ill persons who are not admitted to psychiatric wards. The scale has two scores, HADS-A and HADS-D, and consists of seven questions to assess anxiety and seven questions to assess depression [24]. The scale is focused on psychological symptoms of mood disorders, leaving out physical symptoms that can be confused with physical illness. This is an advantage in populations with cardiac disease where symptoms such as dizziness, dyspnoea or palpitations might be related to the underlying cardiac disease and not to a potential mood disorder [25].

Psychological distress is associated with reduced QoL. Therefore, these patients’ QoL is monitored by a validated questionnaire, the HeartQoL disease-specific questionnaire. The HeartQoL measures health-related QoL in patients with heart disease. It consists of 14 items and provides two subscales: a 10-item physical subscale and a 4-item emotional subscale, which are scored from 0 to 3. Higher scores indicating better QoL [26, 27].

### Usual care

Our usual CR programme consists of a supervised 8-week outpatient exercise intervention at the hospital with 2 weekly sessions of 1.5 h with high-intensity intervals (80% of peak oxygen uptake) and resistance training. The programme is complemented with a weekly session of group-based patient education for 1.5 hours on heart disease, psychological issues and diet counselling. When needed, patients also have one or more individual sessions with a cardiologist, dietician or a nurse.

### Intervention

In addition to our usual CR programme, the intervention group will receive CBT as described below.

### Cognitive behavioural therapy (CBT) background

CBT is an established and recognized evidence-based psychotherapeutic method based on clinical experience, theory and research. Three categories of CBT exist. The first originates from behavioural therapy; the second rests on theories about thoughts and their influence on the body, emotions and actions (cognitive therapy), while the third CBT category (such as acceptance and commitment therapy (ACT), metacognitive therapy and mindfulness-based therapy) is based on acceptance of one's thoughts and feelings. In cognitive therapy, focus is on which of the patient’s thoughts and behavioural patterns may create and maintain current problems and influence functional levels. By changing thoughts and patterns of behaviour, the level of functioning and/or QoL may also be changed [28, 29]. In ACT, the focus is rather on accepting the current situation combined with a commitment to change inappropriate behaviour. In this context, focus is given to the purpose of one’s thinking rather than to the contents of a given thought. CBT and ACT have much in common; they both focus on the present and private internal experiences, and they both present the patient with skills that can be applied in different contexts. Because they share these characteristics, it is possible and even helpful to integrate the two approaches. In the present study, sessions 2, 3, and 5 are based on concepts of changing thoughts and behaviours (CBT), and sessions 1 and 4 are primarily based on ACT interventions [30].

### CBT intervention

The CBT intervention is a psycho-educational group course conducted as five sessions led by an experienced nurse under the supervision of a psychologist who is a specialist in CBT. There will be 3–4 patients in each group for the therapy sessions. Each session will last 2 h and has a set structure, with the use of homework and always ending with the opportunity to give feedback [28].

The five sessions contain:
Introduction to CBT and mapping of own valuesAnxiety and anxiety reduction techniquesFunctional analysis (awareness of consequences of own behaviour)Concerns and strategies for dealing with concernsBalance between requirements and forces as well as conclusion

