### Primary outcome

The primary outcome is mean (method of aggregation) change (metric) in psychological distress (domain) measured by HADS total score (specific measurement) from baseline to three months (time) in the intervention group compared with the usual care group. This outcome may be subject to ascertainment bias when blinding is not possible, e.g. social desirability bias causing participants to respond more favourably. We have attempted to limit this by administering the paper questionnaires to be filled in unsupervised. Furthermore, since both the intervention and the control group receive usual CR in the same cardiac settings, both groups may be subject to similar social desirability bias. At the 6-month follow-up, we anticipate that this bias will be reduced.

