## Trial status

The study is currently enrolling patients and was planned to complete patient enrolment in 2021. However, due to the COVID-19 pandemic, the study is now expected to be extended until 2022. Due to the lockdown in Denmark, it was not possible to include patients from 11 March 2020 until 1 June 2020. The patients randomized immediately before this period had to be excluded as the time until start of the intervention was too long.

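### The 3-month HADS is counted from a pre-randomisation baseline with no allowance for the wait while a CBT group of 3–4 fills, so some CBT patients may be assessed before therapy is complete

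*Protocol article*

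**What the plan says.** Four elements of the protocol article bear on this point.

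- **Allocation is individual.** Under Trial procedure and randomization, "an informed consent form is signed and the patient is randomized to either (1) CR and intervention consisting of five sessions of CBT", the alternative being CR alone. The abstract says "Patients will be randomized 1:1 at three different sites". Blocks are small: "permuting random block sizes of 2, 4 and 6, respectively, is used for randomization". At 1:1, one block therefore yields one to three CBT allocations.
- **Therapy is given in groups.** CBT intervention: "There will be 3–4 patients in each group for the therapy sessions". The five sessions have a fixed order, and the fifth returns to the matrix begun in the first, which points to closed groups.
- **The schedule shows no gap.** Table 1 places the sessions at 0, 1, 2, 3 and 4 weeks.
- **The endpoint clock starts before allocation.** Baseline data are collected before randomisation, and the primary outcome is the change in HADS total "from baseline to three months (time) in the intervention group compared with the usual care group".

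Trial status adds that patients randomised just before the 2020 lockdown were excluded because they would have waited too long for therapy. The same section says enrolment "was planned to complete patient enrolment in 2021", and that the study is now expected to run until 2022.

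**The concern.** Session 1 can fall at time 0 for every member of a group only if all three or four are allocated together. Individual randomisation does not arrange that. Whoever joins first waits for the rest, and that wait uses up part of the 3 months between baseline and the primary HADS.

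A CBT patient measured before finishing therapy still counts fully in the CBT arm, which pulls the contrast towards zero. A null 3-month result could then mean that CBT does not work, or that some patients had not yet received it.

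The planned analyses do not clearly separate these two explanations. The per-protocol set counts sessions attended, not when they took place. The 6-month HADS is collected, but it is not listed as a between-arm outcome, and Statistical analysis uses it as an adjustment variable in the primary model.

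**Working it through.** **The plan's own figure.** A difference of 2, SD 4, two-sided alpha 0.05 and 64 per arm give a t-test power of 0.801. Then 64 × 1.15 = 73.6, rounded up to 74, and 74 × 2 = 148. The stated sample size reproduces, and it agrees with Participants: "The main trial includes 148 randomized patients".

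**Time available.** Sessions run from week 0 to week 4, which is 28 days or 0.92 months. To finish by 3 months, a patient must start within 3 − 0.92 = 2.08 months of baseline.

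**Pace.** None is stated. Two dates bound it, reading the extension to 2022 as applying to enrolment. The latest possible start is the retrospective registration on 30 January 2020, and the earliest end is 1 January 2022. Removing the 82-day pause (11 March to 1 June 2020) leaves 620 days, or 20.4 months. This is the shortest period and so the fastest average pace. With 74 CBT patients:

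- over all sites: 74 / 20.4 = 3.63 per month
- per site, assuming three equal sites: 1.21 per month

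**Model (assumptions).** Arrivals are steady and random (Poisson), groups are closed, and each group starts when full. A member with k others still to come is late with probability e^(−x) × (sum of x^i / i! for i = 0 to k − 1), where x = rate × 2.08.

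**Groups formed within site, 20.4 months.** x = 1.21 × 2.08 = 2.52.

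- k = 1: 0.081; k = 2: 0.283; k = 3: 0.539; the last to join is never late.
- Groups of 3: (0.283 + 0.081 + 0) / 3 = 12%, about 9 of 74.
- Groups of 4: (0.539 + 0.283 + 0.081 + 0) / 4 = 23%, about 17 of 74.
- Mean wait of the first member: 2 / 1.21 = 1.65 months (groups of 3) or 3 / 1.21 = 2.48 months (groups of 4).

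**Other cases, same formula**

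| Group formation | Active months | CBT patients per month per unit | Late, groups of 3 | Late, groups of 4 |
|---|---|---|---|---|
| Within site | 20.4 | 1.21 | 12% | 23% |
| Within site, to 31 Dec 2022 | 32.3 | 0.76 | 24% | 38% |
| Pooled over sites | 20.4 | 3.63 | 0.2% | 0.6% |
| Pooled, to 31 Dec 2022 | 32.3 | 2.29 | 2% | 5% |

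An earlier start than 30 January 2020 would lower the pace and raise every figure.

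**Effect on the contrast** (within site, 20.4 months, true difference 2, 64 per arm)

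- Late patients have half the effect: 2 × (1 − 0.121 / 2) = 1.88, power 0.75; 2 × (1 − 0.226 / 2) = 1.77, power 0.70.
- Late patients have no effect yet: 1.76, power 0.69; 1.55, power 0.58.

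**The case against.** The strongest reply is that the size rests on rules the article does not state. It does not say that groups form within a site or that they wait until full, and it gives no accrual rate. Pooling the three departments nearly removes the problem at the fastest pace, and starting groups short or recruiting in clusters would also shrink it. This stands, so the figures are conditional. Delivery by CR nurses within hospital-based CR makes site-level groups the more natural reading, but not an established one.

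A group-forming rule may also sit in the full protocol or the treatment manual. Its absence from a condensed article is not the point here. The point is that Table 1 and the baseline clock, as printed, leave no room for any wait.

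The likely loss is also modest. At half effect and the fastest pace it is 0.12 to 0.23 points, against a standard error of 4 × √(2/64) = 0.71. Late here means short of all five sessions; many of those patients would have had some. That stands too.

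Flexible follow-up dates might absorb some of the wait. But if visits move only for late CBT patients, the arms are assessed at different times.

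A reader might infer that part of the CBT arm will certainly be unfinished at 3 months, or that group size, schedule and clock cannot all hold. The documents do not support either: they state no enrolment pace, and pooled groups could fit. The Trial status exclusion shows that randomised patients could still be awaiting therapy. However, the lockdown prolonged that wait, so it does not measure group filling. Nor can delayed CBT be said to miss the 8-week CR programme, because its start relative to the first CR visit is not given.

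**Conclusion.** The concern holds as a mismatch between stated elements, with a conditional size. Individual allocation, therapy groups of 3–4, session 1 at time 0 and a 3-month clock from a pre-randomisation baseline are compatible only if groups fill almost at once, and the article does not say how they would.

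With site-level groups that wait until full, even sites and steady accrual, 12% to 23% of the CBT arm may be unfinished at 3 months at the fastest pace the dates allow, and 24% to 38% if enrolment runs to December 2022. With pooled groups the range is 0.2% to about 5%. The direction is not in doubt: any delay dilutes the 3-month contrast. The likely cost ranges from negligible to a fall in power from 0.80 to about 0.70 at the fastest site-level pace with half effect, and more at slower paces.

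This does not invalidate the primary outcome. It does mean that a null 3-month result could not be read on its own without knowing who had finished therapy.

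**What to change.** - Reconcile Table 1 with Trial procedure and randomization, CBT intervention and Primary outcome, stating how session 1 relates in time to baseline.
- Keep the 3-month primary outcome and individual randomisation.
- Name the between-arm HADS difference at 6 months as the key secondary outcome, and stop using the 6-month value as an adjustment variable. At 6 months the latest start that still allows completion is 6 − 0.92 = 5.08 months after baseline, so far fewer patients could be unfinished.
- Record each CBT patient's first and last session dates, and report the share who had finished by the 3-month HADS.
- State in advance that absence of a CBT effect will not be concluded from the 3-month contrast alone if that share is materially below 100%.

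**Cost.** One added secondary outcome, from data already collected, and two dates per CBT patient. The rest is wording.

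Randomising in batches of 6–8 per centre is not recommended. At 148 / 20.4 / 3 = 2.42 patients per site per month, the first patient would wait on average 5 / 2.42 = 2.1 to 7 / 2.42 = 2.9 months. About 19% to 34% of all patients would then be allocated more than 8 weeks after consent, and a trial already enrolling would have two allocation procedures.

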### Sample size and power calculation

The primary outcome is a change in HADS score at 3 months. A clinically relevant difference between groups would be a reduction in the total sum score of 2. In a previous study [36], the change within each group was normally distributed with a standard deviation (SD) of 2.5. We have here used a more conservative estimate with an SD of 4. Under these assumptions with a risk of type 1 error of 0.05 and a power of 0.8, 64 patients should be included in each group. Due to the risk of dropout of patients included in this type of trial, the total number of patients included is increased by 15% to 148 patients

STATA II, the Ralloc programme is used for randomization, permuting random block sizes of 2,4 and 6.

To assess the spontaneous variation in HADS scores over time, we will investigate a non-randomized group of 40 matched patients (relative to inclusion and exclusion criteria) without signs of psychological distress (i.e. HADS A < 8 and HADS D < 8) at first measurement with re-evaluation after 3 and 6 months. With 64 patients in the usual care arm and assuming a SD of 4 as above, we will have 80% power to detect a difference in change in HADS score (delta HADS) of 2.3 or more between these two groups.

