### Statistical analysis

The primary analysis will be a comparison of the intervention and control group in mixed-models linear regression with robust standard errors with 3-month values as outcome, and baseline and 6 months values will be used as adjustment variables. Analyses will also be adjusted for the centre and tested for treatment-centre interaction. For the analysis of the secondary outcomes return to work (yes/no), HbA1c< 48, BP< 135/85 mmHg, BMI< 30, LDL< 1.4 mmol/l and physical activity, we will also apply repeated measures regression. For adherence to CR (> 80%), we will compare groups by logistic regression adjusting for the centre. For the outcome of re-admission at 12 months, we will compare outcomes across groups with Kaplan-Meier curves and time-to-event analyses (Cox regression) adjusting for age, left ventricular ejection fraction, co-morbidities and risk factors as described above. A two-sided P < 0.05 will be considered statistically significant, and all primary outcome analyses will be performed without knowledge of group allocation.

We will compare the primary outcome in intervention and control groups with the spontaneous variation in the non-distressed subgroup of 40 participants by separate mixed-models linear regression adjusting for baseline values and centre.

The primary reported analyses will be carried out as a modified intention-to-treat as participants with missing data on a primary or secondary outcome will be excluded from the corresponding analyses. The analysis is supplemented with per-protocol analyses defined by participation in ≥ 4 of the 5 group-based sessions. Missing information on other co-variates will be permuted if there is < 20% missing data for the co-variate in question.

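### CBT is given in groups of 3–4, but the primary model and sample size have no therapy-group term; if outcomes correlate within groups and this is ignored, the standard error is too small

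*Protocol article*

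**What the plan says.** The protocol article's abstract states the allocation: "Patients will be randomized 1:1 at three different sites". Under CBT intervention, the experimental treatment is a course of five two-hour sessions led by a nurse, and "There will be 3–4 patients in each group for the therapy sessions". The control arm receives usual rehabilitation without these groups.

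Statistical analysis specifies "mixed-models linear regression with robust standard errors" for the primary comparison, with adjustment for baseline and for centre and a test of treatment-by-centre interaction. Centre is the only grouping factor named. The section does not say what the random effects are or at what level the robust standard errors are clustered.

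Sample size and power calculation takes a target difference ("A clinically relevant difference between groups would be a reduction in the total sum score of 2") and an SD ("We have here used a more conservative estimate with an SD of 4"), and concludes that "with a risk of type 1 error of 0.05 and a power of 0.8, 64 patients should be included in each group". It contains no ICC and no design effect.

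**The concern.** Patients in one CBT group share a nurse, five sessions and two or three fellow patients, so their outcomes may be correlated. At 3.5 per group, 64 to 74 CBT patients form about 18 to 21 groups. Controls have no corresponding structure.

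Centre adjustment removes differences between three sites, but not correlation among the few patients who sit in the same room. Robust standard errors help only if they are clustered on therapy group. A patient-level random effect for repeated HADS measurements does not capture this correlation either.

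If the group is left out and the correlation is positive, the confidence interval for the primary effect is too narrow, the nominal 5% test rejects too often, and the 80% power figure holds only for an ICC of zero.

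**Working it through.** **Inputs from the protocol article.** Difference 2; SD 4; two-sided alpha 0.05 ("A two-sided P < 0.05 will be considered statistically significant"); 64 per arm; group size m = 3–4, with 3.5 as the midpoint. **Assumed:** ICC of 0.02, 0.05, 0.10 and 0.20 (none is given), with the total SD held at 4 in both arms.

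**Step 1: the plan's own figure.** With independent patients, SE = 4 × √(2/64) = 0.707. The two-sample t test then has 80.1% power at 64 per arm and 79.5% at 63. The stated 64 is reproduced, so it contains no allowance for clustering.

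**Step 2: partial nesting.** The design effect applies to the CBT arm only: DE = 1 + (m − 1) × ICC. The true SE is 4 × √((DE + 1)/64). For m = 3.5 and ICC 0.10, DE = 1 + 2.5 × 0.10 = 1.25 and SE = 4 × √(2.25/64) = 0.750.

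**Step 3: type I error if the group is ignored.** This is 2 × (1 − Φ(1.96 × 0.707/SE)). For ICC 0.10 the ratio is 0.707/0.750 = 0.943, which gives 6.5%.

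**Step 4: power with the correct SE**, still with patient-level degrees of freedom.

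| ICC | DE | True SE | Naive/true SE | Type I error if ignored | Power |
|---|---|---|---|---|---|
| 0 | 1.000 | 0.707 | 1.000 | 5.0% | 80.1% |
| 0.02 | 1.050 | 0.716 | 0.988 | 5.3% | 79.2% |
| 0.05 | 1.125 | 0.729 | 0.970 | 5.7% | 77.7% |
| 0.10 | 1.250 | 0.750 | 0.943 | 6.5% | 75.4% |
| 0.20 | 1.500 | 0.791 | 0.894 | 8.0% | 70.9% |

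Across m = 3 to 4, type I error runs from 5.6% to 5.9% at ICC 0.05 and from 6.2% to 6.8% at ICC 0.10.

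**Step 5: simulation** (64 per arm, groups of 4, 40,000 runs). A test that ignores the groups had type I error of 5.3%, 5.6%, 6.8% and 8.3% at the four ICCs. A test based on group means with Satterthwaite degrees of freedom held its level at 4.8% to 5.0%. Its power was 77.6%, 75.9%, 73.0% and 67.4%. This is below the formula for m = 4 (about 79%, 77%, 74% and 69%) because the CBT arm then supplies only 16 groups.

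**Step 6: offsets to the power loss.** The earlier study had an SD of 2.5: "the change within each group was normally distributed with a standard deviation (SD) of 2.5". The variance margin is (4/2.5)² = 2.56, whereas clustering inflates the variance of the difference by (1 + DE)/2, which is 1.06 at ICC 0.05 and 1.25 at ICC 0.20. For m = 3.5, power stays at 80% if the SD is at most about 3.88, 3.77 or 3.58 at ICC 0.05, 0.10 or 0.20. At SD 2.5 it is about 98% even at ICC 0.20. Baseline adjustment also helps: with equal variances it multiplies the change-score variance by (1 + r)/2, where r is the correlation between baseline and 3 months. The documents do not give r. Assuming r from 0.5 to 0.7 and m = 3.5, power at 64 per arm is about 88% to 84% at ICC 0.05, 86% to 82% at 0.10 and 83% to 78% at 0.20.

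Neither offset changes step 3. The SD cancels in the ratio of naive to true SE, so the type I error column stands whatever the SD is.

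**The case against.** **The level of the robust standard errors is not stated.** A fuller analysis plan, not shown, could place it at therapy group. This is fair, and it makes the point conditional. It does not remove the point: the article fixes the outcome, covariates, centre adjustment and interaction test, and centre is the only grouping factor among them. Followed as written, the model has no therapy-group term.

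**No ICC is given, and it may be small.** The groups are small, the treatment is manual-based and supervised by a psychologist, and centre is already in the model. If CBT affects no one, little correlation would remain beyond group composition and shared group experience. All of this argues for the lower end of the assumed range, where the inflation is slight. It does not establish zero.

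**The plan has margin for power.** This stands. The deliberately large SD and the baseline adjustment could more than absorb the loss, so a flat restatement of power at 75–78% would be wrong for the analysis planned. The increase to 148 is a weaker argument: it is reserved for dropout, and 148 × 0.85 / 2 leaves about 63 per arm.

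**Conclusion.** The point holds in conditional form. The design is partially nested, and neither the stated primary model nor the sample size reflects it. If therapy group is ignored and the ICC is positive, the standard error is understated by about 1% at ICC 0.02, 3% at 0.05, 6% at 0.10 and 11% at 0.20, with type I error of about 5.3%, 5.7%, 6.5% and 8.0%. These figures rest on assumed ICCs, 3.5 patients per group, 64 per arm and equal total variance in the arms. The effect is small at low ICC and becomes material from about 0.10.

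A reader might infer that the standard errors are certainly too small, that 80% power will not be reached, or that 148 patients are too few. The documents support none of these. They give no ICC and do not state the cluster level, and the plan's SD of 4 and baseline adjustment leave room for power. What can be said is that the 80% figure is conditional on an ICC of zero under the plan's simple calculation, and that the spare margin in power does not repair an interval computed without the therapy group.

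**What to change.** 1. Record a therapy-group identifier for each CBT patient in REDCap.
2. Specify the primary model as partially nested: a random intercept for therapy group in the CBT arm only, controls as singletons, and Satterthwaite or Kenward-Roger degrees of freedom. If the full analysis plan already does this, say so in the protocol.
3. Present the 80% power as conditional on ICC = 0, and show power over an explicit ICC range (for example 0.02 to 0.20), stating the SD, the baseline correlation and the degrees of freedom used.

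The cost is one data field and a few sentences of analysis text. The downside is a slightly wider interval and a less favourable power figure. No change in enrolment is proposed.
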